## Abstract

**Background:**

Idiopathic normal pressure hydrocephalus is an age-related condition characterized by cerebrospinal fluid accumulation and ventricular enlargement, leading to cognitive decline, gait disturbance, and urinary incontinence. Although shunt surgery is the primary treatment, the optimal surgical strategy remains uncertain, and procedure selection is often not tailored to individual patient characteristics. Notably, no prospective study has directly compared the 3 major shunt techniques (ie, ventriculoperitoneal, lumboperitoneal, and ventriculoatrial).

**Objective:**

This multicenter prospective observational study will aim to generate high-quality clinical evidence by evaluating the effectiveness and safety of the 3 aforementioned surgical options in a real-world setting.

**Methods:**

Patients suspected of having this condition will be enrolled based on characteristic symptoms and imaging findings, with a spinal tap test recommended but not mandatory. Eligible patients will undergo one of the aforementioned surgical procedures.

**Results:**

On the basis of recent data from 11 collaborating institutions in Japan, we estimate enrolling 278 cases: 188 (67.6%) surgical, 100 (36%) nonsurgical, and 10 (3.6%) dropouts. Clinical outcomes will be assessed at baseline; after the tap test (if performed); and at 1 week, 3 months, and 12 months postoperatively. The analyses will explore the associations between outcomes and surgical methods, patient backgrounds, and imaging features. As of May 2025, approximately 60 participants have been enrolled from 11 institutions. Data collection is ongoing and is expected to be completed by December 2026. There will be a 1-year follow-up period. The main study results are anticipated to be published in 2028.

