### Sample Size Calculation

The sample size was calculated based on reports of previous iNPH shunt procedures. On the basis of the iNPH cases at the collaborating research institutions over the past 2 years, 56 (29.8%) VPS, 60 (31.9%) LPS, and 72 (38.3%) VAS procedures are anticipated to be performed, resulting in a total of 188 surgical cases during the 2-year enrollment period. In addition, 100 nonsurgical cases are expected to be included during the same period. Considering a 5% dropout rate during follow-up among the operated cases, the final sample size is estimated to be 278 cases (Figure 1).

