**Figure 1 figure1:**
[figure not shown]
Flowchart of the patient enrollment criteria and overall study design in this multicenter prospective observational study of idiopathic normal pressure hydrocephalus (iNPH). Observation cases are determined based on the patient’s intention, condition, and need for surgery. Shunt procedures (ie, ventriculoperitoneal shunt [VPS], lumboperitoneal shunt [LPS], or ventriculoatrial shunt [VAS]) are selected according to the patient’s clinical status and surgeon’s preference. The target numbers for the shunt procedures were estimated from the number of previous surgical cases. DESH: disproportionately enlarged subarachnoid space hydrocephalus.

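### The abstract gives 278 as the number enrolled, but its own parts come to 288; 278 is the number left after about 10 operated dropouts

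*Protocol article*

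**What the plan says.** The protocol article gives the sample size in two places.

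- **Abstract, Results paragraph:** "we estimate enrolling 278 cases: 188 (67.6%) surgical, 100 (36%) nonsurgical, and 10 (3.6%) dropouts". Here 278 is the number enrolled, and the three counts after the colon read as its parts.
- **Methods, Sample Size Calculation:** the procedure forecast is "56 (29.8%) VPS, 60 (31.9%) LPS, and 72 (38.3%) VAS procedures are anticipated to be performed". The section adds these three counts up to 188 operations over the two years of recruitment. For the other group, "100 nonsurgical cases are expected to be included during the same period". The section then concludes: "Considering a 5% dropout rate during follow-up among the operated cases, the final sample size is estimated to be 278 cases".

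The legend of Figure 1 adds that "The target numbers for the shunt procedures were estimated from the number of previous surgical cases". The counts are therefore a caseload forecast and not the result of a power calculation. Under Outcome Measures, the primary outcome is the 1-year change in mRS after surgery, VAS against VPS and LPS combined, so only operated patients contribute to it.

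**The concern.** The surgical and nonsurgical groups exclude each other, and together they already exceed the total they are meant to make up. Dropouts appear as a third category, although the Methods section takes them from the operated patients. The same figure, 278, is called enrolment in the abstract and the final sample size in Methods, and neither place mentions 288.

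Two numbers are at stake: how many patients the study expects to enrol, and how many operated patients should be available at 1 year. The whole dropout allowance falls on the patients who supply the primary comparison, yet the article never states how many of them should remain.

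**Working it through.** **Inputs** (Sample Size Calculation unless noted): VPS 56, LPS 60, VAS 72; nonsurgical 100; dropout 5%, operated cases only; final sample size 278; abstract percentages 67.6%, 36% and 3.6%.

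**1. Reproducing 278**
- Operated: 56 + 60 + 72 = 188, as stated. The shares of 188 (29.8%, 31.9%, 38.3%) are also correct.
- Expected to enter: 188 + 100 = 288.
- Operated dropouts: 0.05 × 188 = 9.4, rounded up to 10, the count in the abstract.
- Remaining: 288 − 10 = 278 (278.6 without rounding the dropouts).

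The alternatives tried do not give 278:
- 5% off all cases: 288 × 0.95 = 273.6.
- Inflating the operated cases for dropout: 188 / 0.95 = 197.9, so 198, and 198 + 100 = 298.
- Adding all three listed counts: 188 + 100 + 10 = 298.

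So 278 is reproduced as a count after dropout, made up of 178 operated and 100 nonsurgical patients.

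**2. Testing the abstract's breakdown**
- 188/278 = 67.6%, 100/278 = 36.0%, 10/278 = 3.6%. All three printed percentages use 278 as the base.
- Their sum is 67.6 + 36.0 + 3.6 = 107.2%.
- Without the dropouts, the two exclusive groups still give 67.6 + 36.0 = 103.6%.
- The cause is that the numerator 188 includes the 10 dropouts while the denominator 278 leaves them out.

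**3. Figures on a consistent base**

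| Quantity | Calculation | Result |
|---|---|---|
| Expected enrolment | 188 + 100 | 288 |
| Surgical share | 188/288 | 65.3% |
| Nonsurgical share | 100/288 | 34.7% |
| Operated patients left at 1 year | 188 − 10 | about 178 |
| VAS left, if dropout is equal across procedures | 72 × 0.95 | about 68 |
| VPS and LPS left, same assumption | (56 + 60) × 0.95 | about 110 |

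The article gives one overall dropout rate, so the split by procedure is an assumption. Keeping 9.4 unrounded would leave 178.6 operated patients, so 178 or 179 is a matter of rounding.

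**4. The other reading of 188.** If 188 were the number intended to complete follow-up, 198 operations and 198 + 100 = 298 enrolled would be needed. The Methods wording, which speaks of procedures to be performed in the enrolment period, favours 188 operations and hence 288.

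**The case against.** The strongest reply is that the Methods figure is sound. Taken as a count after attrition, 278 follows from the stated inputs. With no required number to inflate, subtracting dropout from a caseload forecast is legitimate. That stands: the demonstrable error is in the abstract, and the Methods section is only unclear about what 278 counts.

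A second reply is that dropouts are a subset of the operated patients, so some overlap in the list is to be expected. That accounts for the 10, but not for 188 + 100 exceeding 278.

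Two stronger readings are tempting, and the article supports neither.

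- **Recruitment will stop at 278 and the operated cohort will fall short.** At the planned mix, a ceiling of 278 would give about 181 operated patients (278 × 188/288) and about 172 after 5% loss. But no closing rule by count is stated. The Study Design section describes enrolment by time, as about 2 years.
- **The primary comparison is presented as having 188 evaluable patients.** The article nowhere calls 188 evaluable at 1 year. It states the dropout rate and count, from which about 178 can be derived. A reader who took 188 by mistake would understate standard errors by a factor of about √(188/178) = 1.03.

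Figure 1 is not shown and the registry entry is not at hand, so neither can be said to repeat the error.

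**Conclusion.** The point holds as a reporting error in the sample size. The abstract labels a post-dropout count as enrolment, breaks it into parts that exceed it, and prints percentages that add to 107.2%. On the article's own inputs, expected enrolment is 288, and about 178 of the 188 operated patients should remain for the 1-year comparison.

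The size is modest: 10 of 288, or 3.5%. The procedure counts and their percentages are unaffected. No power, effect size or interval width is stated that depends on 278. The conclusion assumes that 188 means operations performed, as the Methods wording indicates. The figures of 68 and 110 further assume equal dropout across procedures. It should be corrected because a sample size is a figure readers rely on, but it does not undermine the design.

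**What to change.** - **Abstract, Results paragraph:** give an expected enrolment of 288 (188 surgical, 65.3%; 100 nonsurgical, 34.7%), and say that about 10 of the 188 operated patients are expected to be lost to follow-up. Do not list dropouts as a third category.
- **Sample Size Calculation:** state that 278 is the number remaining after dropout from 288, and that about 178 operated patients are expected for the 1-year primary comparison. If the split is given (about 68 VAS against 110 VPS and LPS combined), state the assumption of equal dropout.
- **Authors to confirm** that 188 counts operations and not completers. If it counts completers, the enrolment figure becomes 298.
- **Check** Figure 1 and the registry entry for the same labelling, and correct them only if they carry it.

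The cost is a short text correction. No study procedure changes.

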**Conclusions:**

Japan is well placed to lead this comparative study with its extensive experience in diagnosing and treating this disease. These findings are expected to provide practical guidance for individualized surgical decision-making and contribute to the global consensus on optimal treatment strategies.

**Trial Registration:**

Japan Registry of Clinical Trials jRCT1040250005; https://jrct.mhlw.go.jp/latest-detail/jRCT1040250005

**International Registered Report Identifier (IRRID):**

DERR1-10.2196/80678

## Introduction

One disease closely related to aging is idiopathic normal pressure hydrocephalus (iNPH) in an aging society. The cause of iNPH is believed to be a disorder of cerebrospinal fluid (CSF) dynamics [1,2], leading to the accumulation of CSF within the cranial cavity and resulting in characteristic brain morphological changes, including ventricular enlargement. The Primary clinical symptoms include cognitive dysfunction, gait disturbance, and urinary incontinence [2-4]. This condition significantly impairs physical and mental function over several years, even up to decades after its onset, causing disruptions in daily life and shortening life expectancy. One study found that the 5-year mortality rate in untreated older patients with iNPH was significantly higher (87.5%) than in an age-matched healthy population (19.1%) [5]. Individuals aged 60 years and older are at risk of developing iNPH. A Japanese epidemiological survey reported that the population aged ≥65 years is approximately 36.2 million, accounting for 29.3% of the total population in 2024 [6]. In addition, the prevalence of iNPH ranges from 0.37% to 2.9% [7-9]. An estimated 12,900 new patients with iNPH visit health care facilities annually in Japan [10], suggesting that the number of potential patients is even higher.

The world’s first guidelines for the management of iNPH were published in Japan in 2004, and several advancements have since been made in the diagnosis and treatment of this condition [11]. The characteristic brain imaging findings are disproportionately enlarged subarachnoid space hydrocephalus (DESH) [11-13]. The tap test, a CSF drainage test, is an important diagnostic tool. These findings also allow for the prediction of treatment efficacy [11,14,15]. Generally, the treatment preferred is shunting, using 1 of the 3 surgical methods: ventriculoperitoneal shunt (VPS), lumboperitoneal shunt (LPS), or ventriculoatrial shunt (VAS). In 2010, the results of the prospective clinical study, Study of Idiopathic Normal Pressure Hydrocephalus on Neurological Improvement (SINPHONI), which investigated the efficacy of VPS for iNPH, were published, demonstrating the effectiveness of VPS [13]. In 2015, the results of the SINPHONI-2 trial, which evaluated the efficacy of LPS for iNPH, showed that LPS surgery yielded results comparable to VPS [16]. However, no prospective studies have reported on the efficacy of VAS for iNPH. Although the third edition of the Japanese iNPH clinical practice guidelines was published in 2020, it does not compare the 3 surgical methods or provide recommendations on which one to choose [17]. Thus, the choice remains at the discretion of individual institutions and surgeons based on their experience and clinical judgment.

This study aims to evaluate and compare the effectiveness and adverse events associated with 3 surgical approaches for iNPH: VPS, LPS, and VAS. It will aim to provide evidence-based guidance for selecting the most appropriate surgical method for iNPH treatment.

## Methods

### Study Design

This multicenter prospective cohort observational study will be conducted from November 2024 to December 2028. The patient enrollment period is planned to run for approximately 2 years, with a follow-up period of 1 year. This study will evaluate and compare the effectiveness and adverse events associated with 3 surgical approaches for iNPH: VPS, LPS, and VAS. The goal is to provide evidence-based guidance for selecting the most appropriate surgical method for iNPH treatment.

### Study Settings

This study plans to register patients from 11 institutions, including Nagoya University Hospital and its collaborating institutions. These institutions were selected through a fair process based on their agreement with the objectives of this study and their capability to provide comprehensive care for patients with iNPH. The iNPH database committee was organized by recruiting core members, including 5 neurosurgeons and 1 neuroradiologist, from Nagoya University Hospital and its affiliated institutions. The committee developed clinical trial plans and will manage and centrally review the data as independently as possible. Specifically, 1 neuroradiologist and 2 neurosurgeons will judge the anonymized images and the observed data of patients who are not involved in their treatment. Timely reminders will be issued to the attending physicians to minimize the risk of missing follow-up data.

### Study Population and Eligibility Criteria

This study will include patients who are suspected of having iNPH based on head imaging and clinical symptoms and who undergo a lumbar puncture tap test. Among these patients, those deemed to require surgical treatment for hydrocephalus will be offered the option to choose 1 of the following procedures: VPS, LPS, or VAS. The diagnostic and treatment algorithm generally follows the third edition of the Japanese iNPH clinical practice guidelines. However, based on previous clinical experience, a small number of patients with an Evans index of less than 0.3 may still exhibit features suggestive of iNPH. To allow for the inclusion of such cases, the callosal angle will be incorporated as an additional imaging criterion. Moreover, the criterion of “normal CSF protein levels” described in the guidelines is not a mandatory requirement in this study; values less than or equal to 100 mg/dL are considered acceptable. The inclusion and exclusion criteria are presented in Textbox 1.

Inclusion and exclusion criteria.
**Inclusion criteria**
Aged 60 to 85 yearsHaving at least 1 of the following symptoms: gait disturbance, cognitive impairment, or urinary incontinencePresents with ventricular enlargement (Evans index >0.3) or a small callosal angle (<90°)Head magnetic resonance imaging or computed tomography showing—DESH (disproportionately enlarged subarachnoid-space hydrocephalus) findings, including narrowing of the subarachnoid space in the high-convexity and midline regions
**Exclusion criteria**
Informed consent cannot be obtainedPresence of a clearly identifiable underlying condition known to cause hydrocephalusA clearly identifiable space-occupying lesion in the craniumSignificant brain atrophy observed due to stroke or trauma.A history of intracranial surgery for neurological disorders, excluding minor procedures (eg, evacuation of chronic subdural hematoma).The presence of systemic diseases (such as heart failure, respiratory failure, liver failure, or kidney failure) or cancer that makes the participant unsuitableThe participant deemed unsuitable by the principal investigator or study collaborators

### Sample Size Calculation

The sample size was calculated based on reports of previous iNPH shunt procedures. On the basis of the iNPH cases at the collaborating research institutions over the past 2 years, 56 (29.8%) VPS, 60 (31.9%) LPS, and 72 (38.3%) VAS procedures are anticipated to be performed, resulting in a total of 188 surgical cases during the 2-year enrollment period. In addition, 100 nonsurgical cases are expected to be included during the same period. Considering a 5% dropout rate during follow-up among the operated cases, the final sample size is estimated to be 278 cases (Figure 1).

**Figure 1 figure1:**
[figure not shown]
Flowchart of the patient enrollment criteria and overall study design in this multicenter prospective observational study of idiopathic normal pressure hydrocephalus (iNPH). Observation cases are determined based on the patient’s intention, condition, and need for surgery. Shunt procedures (ie, ventriculoperitoneal shunt [VPS], lumboperitoneal shunt [LPS], or ventriculoatrial shunt [VAS]) are selected according to the patient’s clinical status and surgeon’s preference. The target numbers for the shunt procedures were estimated from the number of previous surgical cases. DESH: disproportionately enlarged subarachnoid space hydrocephalus.

### Outcome Measures

The primary outcome is the change in the Modified Rankin Scale (mRS) score from baseline to 1 year after surgery in the VAS group compared to the VPS+LPS group.

The secondary outcomes are mentioned subsequently. First, the change in the mRS score from baseline to 1 year after surgery in the VAS group will be compared with that in the VPS group. Second, the change in the mRS score from baseline to 1 year after surgery in the VAS group will be compared with that in the LPS group. Third, the change in the mRS score from baseline to 3 months after surgery in the VAS group will be compared with the VPS+LPS group. Fourth, the occurrence of adverse events at 3 months and 1 year after surgery in the VAS group will be compared with the VPS+LPS group. Fifth, the evaluation items influencing treatment decisions in surgical versus nonsurgical cases will be compared.

### Data Collection

The attending physicians and supporting medical staff will document the patient data in an electronic file for registration. During the registration process, interviews will be conducted to collect each patient’s baseline information, including physical examination findings, comprehensive medical history (with specific items, such as previous abdominal surgery and spinal disease), lifestyle habits, and medication history. These variables will be systematically included in the electronic registration form for all patients, allowing the assessment of whether such factors influenced the choice of shunt procedure (ie, VPS, LPS, or VAS) in subsequent analyses. The information mentioned subsequently will be recorded during the treatment and follow-up.

Physical and cognitive function assessments include mRS, 3-m Timed Up and Go Test, Mini-Mental State Examination, and Idiopathic Normal Pressure Hydrocephalus Grading Scale.

The subjective assessment includes questionnaire survey. The objective assessments include (1) CSF opening and closing pressure and its drainage volume during the lumber tap test, (2) general CSF laboratory data, (3) head computed tomography imaging, (4) head magnetic resonance imaging or magnetic resonance angiography, (5) shunt valve pressure settings, and (6) adverse events.

The questionnaire survey that will be used in this study is an original tool for assessing patient-oriented outcomes. It consists of simple questionnaires regarding gait, cognitive and urinary functions, sleep, activities of daily living, and surgical satisfaction (Figure 2). The questionnaire uses a 4-choice ordinal scale to ensure that people with cognitive impairment can easily and reliably select the options. These forms will be completed as self-assessments by the patients and their family members.

**Figure 2 figure2:**
[figure not shown]
Patient home assessment form used in this multicenter prospective study of idiopathic normal pressure hydrocephalus. This questionnaire-based assessment tool, completed by patients and their families, enables the evaluation of the subjective changes after the tap test or shunt surgery. The form consists of 6 categories: gait, cognition, urination, snoring, caregiving, and overall satisfaction with the surgery.

### Surgical Decision and Procedures

The decision to perform shunt surgery is comprehensively determined based on the patient’s intention, condition, and the need for surgery. The reasons for the decision to undergo surgery will be documented. When shunt surgery is planned, the choice of procedure (ie, VPS, LPS, or VAS) will be determined based on the patient’s condition and the surgeon’s preference and technique. The type and configuration of the shunt system, including the choice of the catheter, valve, and valve pressure settings, will also be left to the discretion of each surgeon. However, the use of programmable valves equipped with antisiphon or antigravity devices is strongly recommended to minimize the risk of CSF overdrainage. Neither the manufacturer nor the model of the shunt system is specified in the study protocol. As CSF overdrainage after shunt surgery reportedly correlates with patient height, the height and weight of all patients will be recorded in the registry to allow for post hoc analysis of the relationship between body size and drainage volume. This study will provide no instructions or guidance regarding the surgical techniques or procedures.

### Imaging Analysis

Head computed tomography and magnetic resonance imaging scans will be collected as digital data. The analysis will be conducted under the guidance of the department of radiological sciences at Nagoya University Hospital. These imaging data will be quantitatively evaluated using dedicated image analysis software, including measurements of the DESH score, callosal angle, ventricular volume, and brain center-of-mass displacement. The impact of various factors, including patient background, shunt surgery effectiveness, and adverse events, will be analyzed using imaging findings.

### Representative Example of Clinical Protocol

As this is an observational study, there are no restrictions on the clinical guidelines or decisions. However, to avoid variability and confusion among participating institutions, clinical recommendations will be provided to each institution, and actual clinical practice may be conducted based on these recommendations. The recommended protocol was developed in accordance with the guidelines for the management of iNPH published by the Japanese Society of Normal Pressure Hydrocephalus. It incorporates the active use of the tap test. The guidelines recommend evaluating patients before and after the tap test, within 1 week, and at 3 and 12 months after shunt surgery (Figure 3).

